#### Participants

Patients are eligible according the inclusion and exclusion criteria presented in Table 1*.* The sample was recruited from patients with wounds treated in one of the health care centres engaged in the study.

**Table 1 Tab1:** REOX trial inclusion and exclusion criteria

Inclusion criteria	Exclusion criteria
• Patients over 18 years of age • Patients with leg ulcers (venous, ischaemic, traumatic or diabetic foot ulcer) • Patients with dehisced surgical wounds healing by second intention • Patients with pressure ulcers • Wound area between 1 and 250 cm^2^ (wounds larger than 250 cm^2^ are very unusual and outside the scope of this kind of treatment and therefore we decided to exclude it since such a large wound could be more difficult to heal)	• Systemic inflammatory disease or oncological disease • Wounds with clinical signs of infection • Terminal situation (life expectancy less than 6 months) • Ulcers from other aetiologies: tumours, infectious • Wounds treated with negative pressure therapy • Pregnancy • History of sensitivity or allergy to any of the components of the study dressing

In addition, the following criteria for withdrawal from the study will be considered: 1) worsening of the wound according to the clinical judgment of the professional (appearance of clinical signs of infection or others); 2) appearance of allergies or hypersensitivity to the dressing; 3) death; 4) hospital admission that interrupts the treatment in the primary health care centre; and 5) change in the patient’s residence if the new residence is at a different health centre.

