#### Sampling

Sample size was estimated based on two possible outcomes. First, to detect a difference of 2 points in the RESVECH 2.0 scale mean scores [37] between the intervention and the control group with a standard deviation of 2.0 (5% type 1 error and 20% type 2 error) based on data published by Castro et al. who found a reduction of 8 points in RESVECH 2.0 at 4 weeks of treatment (this is a 23% reduction) [24]. We used a 2-point reduction for sample estimation as the minimum clinically significant difference, and so the study was powered enough to detect just this small difference. The required sample size for this is 17 patients per group. Second, the time to achieve a 50% reduction of the wound area, estimating an average of 49.5 days in the control group and 30.0 days in the intervention group with a standard deviation of 20.0 days (5% type 1 error and 20% type 2 error), as based on the study by Lee [38]. The required sample size for this is 18 patients per group.

An additional 30% is added to compensate possible loss of patients in follow-up, and so the final sample size is 54 patients (27 patients in each group). It is expected that each one of the three health care centres will recruit 18 patients for the study.

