### Data analysis plan

A researcher who is blinded to group allocation will perform the data analysis. All analyses will be performed with SPPS Statistics software (IBM Corp., Armonk, NY, USA). Data will be expressed as frequency and percentages for categorical variables, and mean, standard deviation, range and median for quantitative variables depending on the distribution (normality will be checked with the Shapiro–Wilk test). The statistical significance level will be set at *P* < 0.05.

For the primary outcome of improvement in wound healing the wound area reduction at 8 weeks in the intervention group compared with the standard care group will be tested by a difference of means test. The increase in RESVECH 2.0 [37] score at 8 weeks between both groups will be examined by a difference of means test (*t* test for independent groups or Mann–Whitney test depending if variables adjust to a normal distribution). The effect size will be estimated by Cohen’s *d* statistic. In addition, a repeated-measures analysis (analysis of variance or Friedman test) and a survival analysis (Kaplan–Meier) will be used to analyse the evolution over time.

For secondary outcomes, proportions and categorical variables will be tested using a chi-squared test, and continuous variables will be tested using a mean difference test (parametric or nonparametric).

Analyses will be performed between groups as randomized (an intention-to-treat analysis). Missing data for the outcomes will be tested if they are missing at random; otherwise the last observation carried forward approach will be used for imputation [43]. Furthermore, sensitivity analyses over all the completed cases (a per-protocol analysis) will be performed to check for inconsistencies.

A subgroup analysis by wound type will also be performed to explore whether the effect of the intervention differs for any type of wound according to its aetiology. Moreover, another subgroup analysis by primary care centre will be carried out to check if there are any differences in outcomes according to the centre.

No interim analyses or formal stop-study rules are planned; no harmful problems are anticipated for patients because this new dressing has been previously tested in a series of patients with wounds of various aetiologies without any serious adverse effects [35].

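### Missing outcomes are handled through a test of 'missing at random' that observed data cannot perform, with last observation carried forward as the fallback where it is least justified

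*Protocol article*

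**What the plan says.** The Data analysis plan of the protocol article first commits to comparing the arms as allocated: "Analyses will be performed between groups as randomized (an intention-to-treat analysis". The next sentence gives the rule for missing values: "Missing data for the outcomes will be tested if they are missing at random; otherwise the last observation carried forward approach will be used". It does not say what is done when the data are judged to be missing at random. The only sensitivity analysis is described as "sensitivity analyses over all the completed cases (a per-protocol analysis) will be performed to check for inconsistencies".

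The primary comparisons are mean differences between arms at 8 weeks (t test or Mann-Whitney test) for RESVECH 2.0 change and wound area. For the course over all visits the plan adds: "a repeated-measures analysis (analysis of variance or Friedman test) and a survival analysis (Kaplan–Meier) will be used to analyse the evolution over time".

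Three other places bear on how outcomes go missing:

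- **Participants**: the withdrawal criteria include "worsening of the wound according to the clinical judgment of the professional", with signs of infection as an example.
- **Randomization and blinding**: neither the patient nor the clinical nurse is blinded. Only the assessor of the photographs and the data analyst are.
- **Sampling**: "An additional 30% is added to compensate possible loss of patients in follow-up", giving 54 patients, 27 per group.

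**The concern.** The rule makes the primary result depend on a gate that the data cannot operate. Whether outcomes are missing at random or not at random depends on the values nobody saw. Available tests ask only whether leavers differ from stayers in what was recorded, which is a question about missing completely at random. A significant result is compatible with MAR, and a non-significant one is compatible with outcome-driven loss.

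The fallback is then LOCF, used exactly where loss is judged to be non-random. LOCF assumes that a wound stays as it was at the last visit. In a trial of healing over 8 weeks, an early leaver is given credit for only part of the expected change, so unequal exit rates or exit times turn into an apparent treatment difference.

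Outcome-linked and unequal loss is plausible here, because worsening is a ground for withdrawal and is judged by staff who know the treatment. The completed-case sensitivity analysis does not probe such loss.

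**Working it through.** **Inputs from the protocol article.** RESVECH difference 2 points, SD 2.0, 5% and 20% error rates, 27 per arm, 30% allowance for loss (Sampling); visits at weeks 2, 4, 6 and 8 (Data collection and management). The plan gives no figure for the effect of its missing-data rule. Its sample sizes do reproduce: the two-sided t-test calculation gives 16.7, so 17 per group, for RESVECH and 17.5, so 18 per group, for time to 50% area reduction. A 30% loss would be 0.30 × 54 = 16.2, about 16 patients.

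**Assumptions (not in the documents).** No true effect. Mean improvement linear to 8 points at week 8, that is 2, 4, 6 and 8 points at the four visits. Exits unrelated to outcome and spread evenly after weeks 2, 4 and 6.

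**Step 1: bias of LOCF, by hand.** A patient leaving after week 2, 4 or 6 forgoes 6, 4 or 2 points, on average (6 + 4 + 2)/3 = 4 points. The false difference is (control exit rate − active exit rate) × 4:

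- 40% versus 20%: 0.20 × 4 = 0.80 points, which is 40% of the 2-point difference the trial is sized for.
- 35% versus 25%: 0.10 × 4 = 0.40 points.
- 30% versus 30%, same timing: 0.

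**Step 2: false-positive rate of LOCF, by hand for 40%/20%.** Take SD 2.0 at every visit. The variance of the forgone points is p(36 + 16 + 4)/3 − (4p)².

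- Control: 0.4 × 18.67 − 1.6² = 4.91, total 4 + 4.91 = 8.91.
- Active: 0.2 × 18.67 − 0.8² = 3.09, total 7.09.
- Standard error: √((8.91 + 7.09)/27) = 0.77. Standardised shift: 0.80/0.77 = 1.04.
- Against a critical value of about 2.01, the rejection rate is about 17%.

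**Step 3: simulation** (10,000 trials per row, correlation 0.7 between adjacent visits, falling with distance; the ranges in the first two rows cover constant SD and SD growing to 2.0 at week 8).

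| Exits, control / active | LOCF false difference | LOCF false positives |
|---|---|---|
| 40% / 20% | 0.80 | 18% to 19% |
| 35% / 25% | 0.40 | 8% |
| 30% / 30%, same timing | 0.01 | 5% |
| 40% / 20%, plateau after week 4 | 0.26 | 6.5% |

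The plateau row takes mean improvement of 4, 8, 8 and 8 points. By hand, the average forgone is (4 + 0 + 0)/3 = 1.33 points, and 0.20 × 1.33 = 0.27. A separate run gave 0.28.

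**Step 4: LOCF when there is a true effect.** Assume improvement of 6 versus 4 points, a true difference of 2.0. With linear healing and evenly spread exits, each leaver forgoes half of the final improvement. At 30% loss in both arms the LOCF difference is 2.0 × (1 − 0.30 × 0.5) = 1.70; simulation gave 1.68 to 1.71. So equal loss is harmless under the null but dilutes a real effect.

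**Step 5: the whole gated rule.** Let the gate be a 5%-level comparison of week-2 scores between leavers and stayers, with completers analysed when it passes. Both choices are assumptions, since the plan names neither. Under the 40%/20% scenario LOCF is then triggered in about 5% of trials, and the overall false-positive rate is 5% to 6%.

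**Step 6: the passing branch.** The named week-8 t test or Mann-Whitney test needs a week-8 value. Unless something else is specified, it uses only patients who have one. The classical repeated-measures analysis of variance and Friedman test likewise need complete rows. None of the named tests uses the partial records that a valid analysis under MAR relies on.

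**The case against.** The strongest objection is that the size of the problem is easily exaggerated. A reader might infer that the trial's type 1 error is about 18%. The documents do not support that: the figure is for LOCF applied to every trial, whereas the plan applies it only when its test fails, and Step 5 shows a rate near the nominal level when exits are unrelated to outcome. A still larger figure, 1.2 false points with false positives of about one in three, arises if 30% leave each arm but all control leavers go after week 2 and all active leavers after week 6. Nothing in the documents suggests such a pattern. The linear curve is also an assumption. The Sampling section cites an 8-point change at 4 weeks, and an early plateau cuts the bias by about two thirds. This part of the objection stands.

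A reader might also infer that the plan states a completers-only analysis and so contradicts its own intention-to-treat commitment. It does not say so. Listing completed cases as a separate sensitivity analysis suggests that something else was meant for the main analysis, and an article may leave that method to a fuller document. The passing branch is unspecified, not wrong as written.

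Nor is LOCF always the worse choice. Under simulated MAR exits linked to poor progress in one arm, its bias was −0.27 points against +0.42 for completers. For wounds that heal before week 8, carrying the healed state forward is correct. Finally, the 30% is an allowance for possible loss, not a forecast.

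None of this rescues the gate or the choice of LOCF as the remedy for non-random loss. The article itself fixes both, so they are not details left to an analysis plan.

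**Conclusion.** The concern holds in a limited form and should be fixed. The rule rests on a test that cannot distinguish the two conditions it is meant to separate, and its fallback does not correct the loss that triggers it. When LOCF is applied, the false difference is about 0.8 points at 40%/20% exits and 0.4 at 35%/25%. It is about 0.3 at 40%/20% with an early plateau, and zero under the null with equal loss and equal timing. These sizes rest on the assumed healing curve, exit pattern and SD. They describe LOCF alone, and the documents do not allow an error rate for the full rule. The gap in the passing branch and the lack of a sensitivity analysis for outcome-linked loss add to the case for a single prespecified method.

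**What to change.** In the Data analysis plan:

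1. Delete the test of missing at random and the LOCF fallback.
2. Prespecify one analysis of all randomized patients using all visits, whatever the missingness pattern. Use a likelihood-based repeated-measures model with arm, visit, arm × visit, baseline value and centre, reading the arm difference at week 8. Multiple imputation by arm from the earlier visits is an acceptable alternative.
3. State that wounds healed before week 8 enter later visits with their known healed state.
4. Add a delta (tipping-point) sensitivity analysis that makes the imputed week-8 values of patients withdrawn for worsening or infection progressively less favourable until the conclusion changes. This is needed because a model valid under MAR does not by itself address outcome-linked loss.

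The cost is some rewording and a few lines of syntax in the software already named (a mixed-model procedure is available there). No extra patients or visits are needed, since weeks 2, 4, 6 and 8 are already collected. The confidence interval may be slightly wider than the artificially narrow one from single imputation.

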### Randomization and blinding

Patients (*n* = 54) will be randomized into an intervention group (antioxidant dressing) or control group (standard clinical practice using dressings that create a moist environment). The block randomization scheme was generated using the EPIDAT software. Participants will be randomized to receive antioxidant dressing or standard wound dressing with a 1:1 allocation ratio (Fig. 2) using stratified block randomization with a fixed block size per centre. Once the patient has agreed to participate and has been shown to meet the inclusion criteria, the clinical nurse will open opaque closed envelopes sequentially numbered containing a sheet (folded four times) with the group allocation. Neither the patient nor the clinical nurse is blinded to the treatment received; the data and the wound pictures will be codified and the assessor who evaluates the wound pictures and the data analyst will be blinded to the treatment.

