### Data collection and management

Participants eligible for study entry will be given a unique, sequential, centre-specific study identifier. Clinical data will be entered into paper-based case report forms. After each assessment, the data will be handled according to internal procedures and stored in a secure server. These files will be backed-up into a password-protected environment. Hard copies will be stored locally, in compliance with the Spanish Data Protection Law (2018).

Each patient included in the study will be assessed by one clinical nurse at baseline and every 2 weeks (weeks 2, 4, 6 and 8). Figure 1 shows the variables collected at each assessment. The follow-up of patients in both groups will be continued until week 8 or until complete healing of the wound if this occurs earlier. A follow-up of 8 weeks was considered adequate for this study since the main action of the antioxidant dressing being evaluated is to reactivate the healing process by avoiding the excess of ROS; according to a previous study published by Castro et al. [35], a significant number of wounds improved by the fourth week. In order to promote participant retention and complete follow-up, the nurse will monitor patients in the health care centre. Furthermore, the principal investigator will have the primary responsibility for study monitoring; a formal data monitoring committee is not considered necessary because there is no access to protected information and there is no personal information recorded.

To monitor wound healing, several variables will be used: 1) wound area by direct measurement of length and width with a graduated ruler (Kundin method) [39]; 2) wound area estimated using digital photography with Helcos software [40, 41]; this software is an integrated wound management system, which allows for estimation of the wound area and the relative percentage of tissue types in the wound bed (granulation, slough and necrotic tissue); and 3) the RESVECH 2.0 scale score for chronic wound healing [37] (this scale assesses six aspects — wound size, depth/affected tissues, wound edges, type of tissue in the wound bed, exudate and infection/inflammation — with a higher score showing more improvement in the healing process from 0 (the worst possible status of the wound) to 35 points (wound healed)).

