### Outcomes

The primary outcome is the improvement in wound healing with two end points: 1) an increase in the RESVECH 2.0 scale score [37] (score at baseline minus score at 8 weeks); and 2) a reduction in the wound area (area at baseline minus area at 8 weeks). The RESVECH 2.0 score includes the assessment of the wound area, but we also decided to use the reduction in wound area as a specific end point to have a direct measurement of wound size (despite not estimating the sample size with this outcome because there were no data available from previous studies). Additionally, the values at 2, 4 and 6 weeks for each end point will be calculated. These end points are chosen for the clinical relevance of the antioxidant dressing because this product is well-known for removing the nonviable tissue (necrotic or devitalized) in the wound bed, for promoting the production of granulation tissue and for activation of the healing process [35, 42].

The secondary outcomes are the time to achieve a 50% reduction in wound area, the time elapsed until removal of nonviable tissue from the wound bed, reduction of the wound area, the number of completely healed wounds, the pain level and the area of the wound with bacterial load (clinical signs of infection or measurement of surfaces containing bacteria).

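### The missing-data rule rests on a missing-at-random test that cannot guide the choice and then falls back on LOCF, so with withdrawal for worsening the week-8 comparison is open to bias

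*Protocol article*

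**What the plan says.** Five statements in the protocol article bear on this point.

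- **Data analysis plan.** The analysis is by intention to treat. Missing outcome data are to be "tested if they are missing at random; otherwise the last observation carried forward approach will be used for imputation". The only sensitivity analysis for missing data uses completed cases and is labelled per-protocol.
- **Participants.** Below Table 1, "the following criteria for withdrawal from the study will be considered". The first is "worsening of the wound according to the clinical judgment of the professional (appearance of clinical signs of infection or others"; the second is "appearance of allergies or hypersensitivity to the dressing". Death, hospital admission and a move to another health centre follow.
- **Randomization and blinding.** "Neither the patient nor the clinical nurse is blinded to the treatment received". The assessor of the photographs and the data analyst are blinded.
- **Data collection and management.** Visits are at weeks 2, 4, 6 and 8. "The follow-up of patients in both groups will be continued until week 8 or until complete healing of the wound if this occurs earlier". No assessment after withdrawal is described.
- **Outcomes.** Both primary end points, RESVECH 2.0 and wound area, are changes from baseline to week 8.

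**The concern.** The rule has three weaknesses.

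1. Whether data are missing at random or not at random depends on values nobody has seen. A test on the observed data can reject missing completely at random, but it cannot support the choice that the plan hangs on it.
2. The fallback is in the wrong place. If the data are judged not missing at random, the plan uses LOCF, which corrects for no such mechanism. If they are judged missing at random, no method is given.
3. The withdrawal criteria can make the loss depend on the outcome. If a worsening wound leaves the study, LOCF may carry forward a value from before the deterioration, and the completed-case analysis leaves that patient out.

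At stake is the week-8 comparison on both primary end points. If one arm loses more worsening wounds than the other, that arm looks better than it is. Such an imbalance is plausible because worsening is a matter of judgement, the treating nurse knows the allocation, and sensitivity to the dressing is itself a ground for withdrawal.

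**Working it through.** **The plan's own figures.** The Sampling section gives a 2-point RESVECH difference with SD 2.0, and 49.5 against 30.0 days with SD 20.0, at 5% type 1 and 20% type 2 error. An exact two-sided t calculation returns 17 per group (power 0.807) and 18 per group (power 0.811), as stated. Allowing for 30% loss, 18 / 0.7 = 25.7, so 26 per group or 52 in all. The stated 54 is close to this and equals 3 centres x 18. The sample size is not at fault.

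**How much data the rule could govern.** 0.30 x 54 = 16.2 patients, about 8 per arm (0.30 x 27 = 8.1). With 27 x 0.7 = 18.9 left per arm, power by the normal approximation is still about 0.87 (RESVECH) and 0.85 (time to 50% area reduction). The allowance therefore protects precision, but it does nothing about bias. The 30% covers loss for any reason; the protocol gives no rate of withdrawal for worsening.

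**Size of the bias (assumptions, not protocol figures).** Let w be the share of an arm withdrawn for worsening, and k the number of RESVECH points by which the carried-forward value overstates the true week-8 improvement, taken as equal in both arms. LOCF overstates each arm's mean by w x k, so

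bias in (intervention minus control) = (w_int - w_con) x k.

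| w_con | w_int | k = 2 | k = 4 | k = 8 |
|---|---|---|---|---|
| 15% | 15% | 0 | 0 | 0 |
| 10% | 20% | 0.2 | 0.4 | 0.8 |
| 5% | 25% | 0.4 | 0.8 | 1.6 |
| 20% | 10% | -0.2 | -0.4 | -0.8 |

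Against the 2-point design difference, the non-zero entries run from 0.2 / 2 = 10% to 1.6 / 2 = 80% in size, with either sign.

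**Effect on the test.** This was simulated with 27 per arm, SD 2.0, a t test at 5% and no true difference among all randomised patients. Rejection rates were:

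- 15% against 15%, k = 4: about 5%
- 10% (control) against 20% (intervention), k = 4: about 11%
- 10% against 20%, k = 8: about 31%
- 5% against 25%, k = 4: about 30%

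In the other direction, with a true difference of 2 points, 25% control against 5% intervention and k = 4, the average estimate is 1.2.

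**Why completed cases do not reveal it.** In this illustration the carried-forward values have the same mean as those of the patients who stay. A completed-case analysis therefore has the same expected difference as LOCF, and agreement between the two would reassure wrongly.

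**The case against.** The strongest reply is that much of the harm is inferred. Several stronger readings are tempting, and the protocol does not support them.

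- **That the estimate is biased.** It is open to bias. If withdrawal shares and carried-forward errors are equal in the two arms, this bias is zero, and the protocol gives no data on either.
- **That measurement certainly stops at withdrawal.** The article does not say so; it only describes nothing afterwards. The full protocol may say more. If the wound is assessed when worsening is found, LOCF carries forward the worsened value and the error shrinks.
- **That early healers count as missing.** Follow-up "will be continued until week 8 or until complete healing of the wound if this occurs earlier", so a healed patient has completed it. The end state is known, and LOCF would give the right value. Only a written statement of that value is wanted.
- **That infection events are lost.** The sign of infection that prompts withdrawal is known when it appears. The secondary outcome is "the area of the wound with bacterial load (clinical signs of infection or measurement of surfaces containing bacteria"; only later measurements of it could be lost.
- **That the test cannot be run at all.** A test of missing completely at random can be run. It cannot justify the decision made from it.

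It is also fair that the proposed mixed model itself assumes missing at random. That is why it needs the sensitivity analysis beside it.

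All of this limits the claim about consequences. It does not rescue the rule, which the article states outright and which a later analysis plan would have to replace, not merely elaborate.

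**Conclusion.** The point holds in this form: the missing-data rule is unsound as written. Its test cannot guide the choice, its fallback is invalid in the case it is reserved for, and the other case has no method. Combined with withdrawal for worsening under unblinded care, it leaves the week-8 comparison open to bias of unknown direction, and the one planned sensitivity analysis would not show it.

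The range of 0.2 to 1.6 RESVECH points is an illustration. It rests on assumed gaps between arms of 10 to 20 percentage points in withdrawal for worsening and assumed carried-forward errors of 2 to 8 points. The criticism of the rule depends on none of these figures.

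**What to change.** **Data analysis plan**

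1. Delete the missing-at-random test and LOCF.
2. Estimate the week-8 difference in each primary end point with a mixed model for repeated measures on weeks 2, 4, 6 and 8 in all randomised patients, and state that it is valid under missing at random.
3. Add a sensitivity analysis that gives patients withdrawn for worsening a delta-shifted value, over a stated range, or a worst-case value. Report withdrawals by arm and reason.
4. State that healed wounds are complete, with area 0 and the scale's healed value at later visits. This assumes no recurrence before week 8.

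**Participants and Data collection and management**

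5. Separate stopping the allocated dressing, which remains a clinical decision and is unchanged, from leaving the study. Continue the scheduled two-weekly assessments to week 8 wherever the patient can be reached.

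**Cost.** Items 1 to 4 change wording and use visits already planned. Item 5 needs a short amendment and a few more scheduled assessments. Recruitment began in September 2019 and this version dates from April 2020, so week-8 data from patients already withdrawn may not be recoverable. Patients who die, are admitted or move may be out of reach. Completion of recruitment was expected in December 2020, so later patients could still benefit.
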